**Fig. 2 Fig2:**
[figure not shown]
Illustration of the videogames used to train the ‘priority’ attentional strategy. **a** Neuropeak dual task; **b** “Tap to Cook”; **c** “Chicken Run”

Music and Spanish activities were selected because the literature on the neuroscience of aging indicated that they may have a neuroprotective effect. Music and Spanish sessions have been created by professional music and Spanish teachers to be ecologically valid, similar to a class that adult beginners would receive in the community. Music sessions include mostly practical exercises; for example, choral singing, introduction to musical composition and song writing, rhythmical exercises (e.g., introduction to drums, light dancing, body percussions) but also some more theoretical elements (for instance, introduction to music notation, visual representation of pitch and rhythm, musical styles, composers, etc.). The Spanish sessions have a similar proportion of practical and theoretical teaching. Most of the sessions contain practical exercises which include an introduction to simple grammatical notions and vocabulary, taught in ecologically valid situations involving simple conversations (e.g., sharing with the group about us, expressing in Spanish where we come from, what we like, what we want to do, etc.), or role playing (e.g., ordering food in a restaurant, asking for directions, etc.), as well as an introduction to some elements of the Hispanic culture worldwide (food, art, etc.).

Music or Spanish sessions alternate with cognitive training (see Table 1) so that the strategy learned during cognitive training can be subsequently applied during the sessions devoted to leisure. The attentional strategy will be applied while playing casual videogames as the three videogames have components of dual tasking. Hence, participants will be asked to prioritize the left or the right hand-side images in the Neuropeak dual task and certain actions over others in the Tap to Cook and Chicken Run games. Memory strategies will be applied in the music/Spanish sessions. For instance, mental imagery will be used to memorize song lyrics and to learn Spanish vocabulary, face-name association will be used to memorize faces of music composers and Hispanic figures, and spaced retrieval will be used to learn the time value of musical notes or irregular verbs in Spanish.

##### Homework

To increase the likelihood of transfer, participants will be asked to complete exercises meant to review and practice the learned strategies by applying them to everyday life situations (about 2 h of homework per week in total). For instance, they will be asked to use the face-name association technique to remember the name of a new person they encounter. Homework will also include music/Spanish exercises to consolidate the concepts learned during the class and to keep applying the memory strategies to the leisure activities. Finally, participants will be asked to practice the attention control strategy on the tablet games (1 h per week).

#### ENGAGE-DISCOVERY

The ENGAGE-DISCOVERY program (Table 2) will be used as an active control. This will be structured in the same manner as the ENGAGE-MUSIC/SPANISH program and will comprise the same number of classes, hours of homework, and ratio of formal classes to leisure activities. The content of the ENGAGE-DISCOVERY program was selected to be less cognitively stimulating than the intervention, yet interesting and enjoyable, to ensure the same level of expectation and participation.

**Table 2 Tab2:** The ENGAGE-DISCOVERY program: class and home sessions

Week	First class of the week		Homework	Second class of the week		Homework
	Hour 1	Hour 2		Hour 1	Hour 2	
1	**Educational-1: Myths and reality about aging; discover your brain**		Formal (60 min)	**Educational-2: Attention and working memory**		Formal (60 min)
2	**Educational-3: Semantic memory**	Videogames: Freecell	Formal (30 min) + Freecell (30 min)	**Educational-4: Episodic memory**	Videogames: Words	Formal (30 min) + Words (30 min)
3	**Educational-5: Memory and senses**	Videogames: Freecell + Words	Formal (30 min) + Freecell (30 min)	**Educational-6: Procedural memory**	Videogames: Freecell + Words	Formal (30 min) + Words (30 min)
4	**Educational-7: Executive functions**		Formal (30 min) + Freecell (30 min)	Documentary and discussion		Reading (30 min) + Words (30 min)
5	**Educational-8: Neuroplasticity**	Documentary and discussion	Formal (30 min) + Freecell (30 min)	Documentary and discussion		Reading (30 min) + Words (30 min)
6	**Educational-9: Nutrition and exercise**	Documentary and discussion	Formal (30 min) + Freecell (15 min) + Equilibrium (15 min)	Documentary and discussion		Reading (30 min) + Words (30 min)
7	**Educational-10: Sleep and stress management**	Documentary and discussion	Formal (30 min) + Freecell (15 min) +Equilibrium (15 min)	Documentary and discussion		Reading (30 min) + Words (30 min)
8	**Educational-11: Health and mood**	Documentary and discussion	Formal (30 min) + Freecell (15 min) + Equilibrium (15 min)	Documentary and discussion		Reading (30 min) + Words (30 min)
9	**Educational-12: Review—different types of memory**	Documentary and discussion	Formal (30 min) + Reading (30 min) + Words (30 min) + (15 min) + Equilibrium (15 min)			
10	Documentary and discussion		Reading (60 min) +Words (30 min) + Freecell (15 min) + Equilibrium (15 min)			
11	**Educational-13: Review—attention and executive functions**	Documentary and discussion	Formal (30 min) + Reading (30 min) + Words (30 min) + Freecell (15 min) + Equilibrium (15 min)			
12	Documentary and discussion		Reading (60 min) + Words (30 min) + Freecell (15 min) + Equilibrium (15 min)			
13	Documentary and discussion		Reading (60 min) + Words (30 min) + Freecell (15 min) + Equilibrium (15 min)			
14	Documentary and discussion		Reading (60 min) + Words (30 min) + Freecell (15 min) + Equilibrium (15 min)			
15	Documentary and discussion		Reading (60 min) + Words (30 min) + Freecell (15 min) + Equilibrium (15 min)			
16	**General review**	General discussion	Not applicable			

Bold typeface corresponds to formal (educational) sessions

During the 17 h of formal classes, participants will receive information on the brain and cognitive processes, the effect of age on cognition, and tips to promote successful aging (diet, sleep, physical activity, etc.). The 31 h of leisure activities will comprise documentaries and discussion as well as low-stimulating casual videogame playing. Participants will be watching and discussing Planet Earth (a TV series produced by the BBC) and Tomorrow (produced by Moviemovie) documentaries which will cover various topics of interest about nature (geography, animals, landscapes, climate, environment). A discussion-debate will follow each documentary where participants will be invited to share their opinion on topics related to the documentary they have seen. This is to ensure that participants have a similar level of interaction as in the music and Spanish classes. In addition, participants will also play videogames on tablets: (1) FreeCell, where participants have to organize cards in series; (2) Words, where participants have to find words hidden in grids; and (3) Equilibrium, where they have to remove pieces from a structure while maintaining its balance. The games selected are entertaining but, unlike the games selected for the active intervention, do not include formal dual-tasking, processing speed, or metacognitive control. Homework will involve exercises related to the information contained in the psychoeducation sessions (e.g., making a sleep journal), as well as playing the three videogames.

### Adherence to treatment and retention

A number of strategies will be used to reduce attrition and promote retention over the 24-month follow-up. The coordinator of the study will be available by phone to discuss potential problems. In case of reduced adherence, we will contact the participant or his/her informant to identify the reasons and/or barriers that reduce their attendance and help identify solutions. The choice of a preference trial where participants are given the possibility to exclude an activity they dislike was also made to increase adherence to treatment. The team will remain in contact with the participants during the long-term follow-up through yearly telephone calls and greeting cards for the festive season. The attrition rate is expected to be approximately 18% based on our most recent study which used a similar program [10]. The characteristics of those who withdraw will be analyzed and intent-to-treat analyses will be used. Participants who withdraw from the program will be invited to come for follow-up assessments.

### Baseline characterization

Different measures will be used at baseline for diagnosis and clinical characterization and for measuring outcomes. Participants will be characterized on a number of psychological, cognitive, and physical variables, as well as past and current lifestyle and activities (please refer to ClinicalTrials.gov NCT03402919 and to Additional file 2: Appendix 1 for a description of the baseline assessments). This will include information on demographics (age, sex, education), occupations and hobbies, social engagement, general health, current and past medication, medical history, family medical history, physical measurements (weight, blood pressure, etc.), neurological examination, blood, saliva and urine collection (and an optional lumbar puncture), screening tests for mild cognitive impairment or dementia, gait evaluation, sensory processing (visual and auditory acuity), smoking and alcohol use, nutritional habits (Canadian Longitudinal Study on Aging (CLSA) Short Diet Questionnaire [43], and abbreviated version of the SCREEN II [44]), physical exercise (Physical Activity Scale for the Elderly (PASE) [45] and California Teachers Study Long Term Recreational Physical Activity Survey [46]), self-perception and psychological state (self-administered questionnaires, including Beck Depression Inventory II (BDI-II) [47] and Beck Anxiety Inventory (BAI) [48]). Biosamples will allow investigation of genetic biomarkers of a high risk of Alzheimer’s disease and of brain plasticity (apolipoprotein (Apo)E4, brain-derived neurotrophic factor (BDNF), and catechol-O-methyltransferase (COMT)). Cognitive reserve proxies will be evaluated using years of education and a modified version of Rami and colleagues cognitive reserve questionnaire adapted for French and English by the CIMA-Q team [32, 49]. As the intervention involves training participants on videogames and music and/or second language learning, the participants prior experience in those areas will be characterized through questionnaires of game literacy (Game Experience Questionnaire, created by our team), computer proficiency (Computer Proficiency Questionnaire (CPQ) [29]), experience with music (Music Experience Questionnaire, created by our team), and multilingualism (Language Experience and Proficiency Questionnaire (LEAP) [50]).

### Outcome variables

Evaluations will be conducted at the Centre for Memory and Aging, Baycrest Health Sciences, and Sunnybrook Hospital for Toronto participants. In Montreal, they will be conducted at the IUGM. Outcome measures will be tested at three time points: before the intervention (PRE; time frame within 12 weeks before intervention starts), just after the intervention at the 4-month follow-up (F4; time frame within 8 weeks after the end of the intervention), and at the 24 follow-up (F24; time frame 2 years after PRE ± 3 months). Participants are not allowed to participate in other research programs or lifestyle interventions between baseline and the first follow-up (F4), but they can get involved in any activities between F4 and F24.

#### Primary outcome measure

The primary outcome measure will be performance on a composite episodic memory score measured at PRE and F4. The composite score will be computed by averaging *z*-scores from the delayed recall of the Rey Auditory Verbal Learning Test (RAVLT) [51] and the delayed recall of the face-name association taken from the CIMA-Q study [32]. The RAVLT consists of learning a list of 15 unrelated words (list A) over five trials, followed by one-trial learning and recall of an interference list (list B). Free recall of list A is tested immediately after recalling list B, and again 20 min later for delayed recall. The score that will be converted into a *z*-score to compute the composite score is the number of words recalled in the delayed trial (maximum score = 15). In the face-name association task, participants learn nine pairs of face + first name associations. They are asked to recall the name associated with the faces and to recognize the pairs among distractors immediately after learning and following a 20-min delay. The score obtained which will be used in the composite score will be the number of names recalled in the delayed trial (maximum score = 9).

##### Psychological health

Four categories of psychological health measures will be taken at PRE, F4, and F24. (1) An anxiety and depression composite score will be calculated from *z*-scores obtained from the Geriatric Anxiety Inventory (GAI) [54] and the Geriatric Depression Scale (GDS) [55]. (2) A score of apathy will be computed by combining results from the participant and informant versions of the Apathy Inventory [56]. (3) Quality of life will be obtained by computing a combined score using the Quality of Life Alzheimer Disease questionnaire (QoL-AD) [57] and the 36-item short-form health survey (SF-36) [58]. (4) Finally, help-seeking behavior will be assessed by the Medical Care section of the Stanford Chronic Disease questionnaire [59].

##### Impact and transfer to everyday life

The impact of the intervention on the everyday life of participants will be measured at PRE, F4, and F24, with both self-administered questionnaires and performance-based tasks. Seven scores will be computed. (1) Self-administered questionnaires on memory functioning will include the Metamemory Questionnaire (MMQ) [60] and will be used to assess the perceptions of participants about their memory, common memory mistakes, and their use of memory strategies. (2) An abbreviated version of the Auto-administered Memory Questionnaire (AMQ) [61, 62] will assess cognitive (memory and attention) complaints. (3) A questionnaire measuring complex activities of daily living, the Alzheimer’s Disease Cooperative Study—Activities of daily living—Prevention Instrument (ADCS-ADL-PI) [63], will be completed by the participants and their informant and will assess the ease with which the participants perform instrumental activities of daily living. A composite score will be calculated for this test by combining both participant and informant scores. (4) Participants will complete the Cognitive Activities Questionnaire, a questionnaire about the amount of cognitive activities performed in everyday life, adapted from Vemuri and colleagues [64]. (5) Jessen’s questions [20] will be asked. The measure that will be used is the number of participants that have a memory concern (i.e., answering “yes” to both of the Jessen questions [20, 21]) at each time point. Performance-based measures will include two measures. (6) In the Memory Toolbox test [39], participants are presented with everyday scenarios commonly encountered and asked to generate memory strategies that would be beneficial. Participants are scored based on the number and appropriateness of the memory strategies generated. (7) The Direct Assessment of Functional Status—Revised (DAFS-R) [65] is a test of instrumental activities of daily living assessing skills in four domains: communication, financial management, shopping, and medication management. The test simulates everyday life activities, such as looking for a telephone number in a phone book and calling this number from an unplugged telephone, preparing a mock cheque or balancing a mock bank account, memorizing a list of things to buy and retrieving these items on a shelf containing empty boxes of food (targets and distractors), preparing a pill box, etc.

##### Brain structure

Hippocampal volume and cortical thickness will be measured at PRE, F4 and F24 for a subgroup of participants (*N* = 54; 27 per intervention condition) at the Montreal site. Participants will be scanned on a Siemens TIM Trio 3-T PRISMA MRI system (Siemens Medical Solutions, Erlangen, Germany) at the Unité de Neuroimagerie Fonctionnelle (UNF) of the IUGM Research center. A structural sequence will be used to measure hippocampal volume (mm^3^) and cortical thickness (mm) since these are early biomarkers of AD [66] and were found to be sensitive to memory training (see, for example, [67]).

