**Fig. 1 Fig1:**
[figure not shown]
Illustration of the study design. *ADCS-ADL-PI* Alzheimer’s Disease Cooperative Study—Activities of daily living—Prevention Instrument; *CLSA* Canadian Longitudinal Study on Aging; *(f)MRI* (functional) magnetic resonance imaging; *V0* Phone screening interview; *V1* First visit (screening); *V2* Second visit (clinical assessment); *V3* Third visit (neuropsychological assessment); *V4* Fourth visit (neuropsychological assessment); *V5* Fifth visit (MRI; includes fMRI for a subgroup of participants); *V6-29* ENGAGE Intervention sessions (24 visits); *V30* 4-month follow-up neuropsychological assessment; *V31* 4-month follow-up MRI/fMRI (for a subgroup of participants); *V32 & V34* 24-month follow-up neuropsychological assessment; *V33* 24-month follow-up clinical visit; *V35* 24-month follow-up MRI. X: administered during the visit; ♦: given to be completed at home by next visit

Participants will be randomly assigned to one of two conditions: the intervention program combining stimulating leisure activities with formal cognitive training (ENGAGE-MUSIC/SPANISH) or an active control condition (ENGAGE-DISCOVERY). As the program is based on the notion that leisure activities are pleasant, and because some people may have strong discomfort with learning music or be reluctant to learn foreign languages, participants will have the option of excluding either the “Music” or “Spanish” activity at their entry in the study. Participants randomized in the intervention (ENGAGE SPANISH/MUSIC) arm who did not exclude one activity will receive either Spanish or music training based on a second independent random assignment. Thus, the intervention versus active control comparison is fully randomized, but secondary analyses comparing the two leisure activities will rely on a partially randomized cohort. Furthermore, and as described below, analyses will first compare the fully randomized cohorts followed by a comparison of the comprehensive cohort, including those in the preference arms.

For all three groups (ENGAGE-MUSIC, ENGAGE-SPANISH, and ENGAGE-DISCOVERY) 24 training sessions will be delivered over a 4-month period. Participants will be assessed at baseline, which will be no more than 8 weeks prior to training (PRE), at 4-month follow-up, i.e., no more than 4 weeks following training (F4), and 24 months after baseline (F24).

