### Procedure

Interested participants will be screened over the telephone to determine eligibility for the study including the presence of a memory complaint with worries. Participants and informants will be presented with the inform and consent form and sign it with the research nurse at the beginning of their first visit (see Additional file 2: Appendices 4 and 5). They will be invited to undergo baseline (PRE) testing that will include two visits for screening and clinical assessment to determine whether participants meet inclusion criteria for cognition (see ‘Study population’ section above), a clinical and physical examination, and biological sampling. They will then be invited to two sessions to complete the neuropsychological assessment and one MRI session (with a functional MRI (fMRI) condition for a subgroup of participants). Finally, an optional session involves a lumbar puncture. After the 24 intervention visits, participants will undergo the follow-up assessment (F4) including a neuropsychological assessment and an MRI/fMRI for a subgroup of participants. All participants will be invited for a last follow-up assessment 24 months after PRE, including clinical and neuropsychological assessment as well as an MRI (see Fig. 1).

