### Randomization and blinding procedure

The opportunity to exclude either music or Spanish training will be offered to all participants prior to randomization. Randomization will be done individually (i.e., one participant at a time as they enter the study) with random lists of binary numbers. Lists will be generated using the Random.org online software. Randomization will be controlled by a person from the Montreal site who is independent of the study. A first randomization will allocate participants to the intervention or control condition by matching the sequential list of participant identification codes with the list of random condition allocation. This will be done with a 2 to 1 ratio between intervention and control conditions. A second randomization will be used to allocate participants in the intervention condition to either Spanish or music training, using a 1 to 1 ratio for participants who did not exclude either of these two activities. Participants randomized in the intervention condition who excluded music or Spanish training will be placed in their preferred activity. Recruiting staff will contact (via telephone) the trial allocation office in charge of randomization once a participant has consented to participate and will be given the allocation. The allocation and sequence of allocation will be concealed from evaluators.

Evaluators who will be assessing the participants will be blinded to the hypotheses and to the group assignment of participants. Participants will be asked not to mention their group assignment to evaluators. Any breach of this group assignment blinding by participants will be noted, but since evaluators will be blinded from the hypotheses this should have minimal effect on integrity. Activity leaders will not be blinded to the study hypotheses. Although participants will know that they are in the Spanish, music, or documentary discussion group, they will not be informed of the study hypotheses, i.e., participants assigned to ENGAGE-DISCOVERY will be unaware that it is an active control condition. To keep participants blinded from the hypotheses and reduce the likelihood that the expectations of participants bias the data [29], close attention will be paid to ensure that the content of the intervention and the wording of recruitment documents and consent forms do not convey the expectations that one condition is inferior in terms of its effect on the brain and cognition.

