### Statistical analyses

#### Sample size

The trial will recruit 144 participants. The sample size was estimated from a power analysis with G*power based on pilot findings collected with the MEMO program [10, 12], using word recall and face-name associations tasks. The MEMO program is included as part of the formal training in this intervention in addition to stimulating leisure activities and attentional training. Therefore, it is reasonable to expect that the effect should be at least as large as the one observed when using MEMO alone. The pilot data indicated a medium effect size for the group-by-time interaction when examining face-name association and a large effect size when examining word recall (see Additional file 2: Appendix 2). It shows that the sample size would be sufficient to detect an interaction given a similar effect size considering the same attrition rate that we obtained in this prior study (18%). Half of the sample will be recruited in Montreal and the other half will be recruited in Toronto.

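### The imaging subset of 27 per condition at Montreal is not expected on the planned numbers: 72 participants randomised 2:1 give about 24 controls

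*Protocol article*

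**What the plan says.** All references are to the Protocol article.

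- **Sample size:** "The trial will recruit 144 participants", and "Half of the sample will be recruited in Montreal and the other half will be recruited in Toronto".
- **Design:** "Participants will be randomly assigned to one of two conditions", the combined Music/Spanish programme or the active control.
- **Randomization and blinding procedure:** "This will be done with a 2 to 1 ratio between intervention and control conditions". On method, "Randomization will be done individually (i.e., one participant at a time as they enter the study) with random lists of binary numbers". No stratification by site is stated.
- **Brain structure:** hippocampal volume and cortical thickness are measured at PRE, F4 and F24 in a subgroup of 54, "27 per intervention condition) at the Montreal site".
- **Brain function:** task fMRI at PRE and F4, also in a subgroup of 54.
- **Procedure and the Fig. 1 legend:** every participant has one MRI session at PRE, with only the fMRI part limited to a subgroup. The F4 scan is for a subgroup. At F24, "All participants will be invited for a last follow-up assessment 24 months after PRE, including clinical and neuropsychological assessment as well as an MRI".
- **Analysis of efficacy and maintenance:** the structural measures enter a mixed model with three time levels. No analysis set is named for them there.

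**The concern.** The balanced 27:27 split is stated for a site where allocation is unbalanced by design. Under 2:1 the control arm limits the subset, and half of a 144-person trial is expected to supply fewer controls than the figure requires. Brain structure and function are named secondary objectives, so the size and make-up of this subset determine the precision of those comparisons.

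There is also a question of selection. A subset drawn from a 2:1 population without regard to arm will tend towards 2:1. A subset at or near 1:1 has to be chosen with knowledge of arm, and the article gives no rule for choosing it.

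**Working it through.** **Inputs.** Total 144 and Montreal share one half (Sample size); allocation 2:1 (Randomization and blinding procedure); two conditions (Design); 54 scanned, 27 per condition (Brain structure).

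**The plan's own figure.** 2 × 27 = 54, so the subgroup total agrees with its split under the two-condition reading.

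**Expected Montreal counts.**
- Montreal: 144 × 1/2 = 72.
- Control: 72 × 1/3 = 24.
- Intervention: 72 × 2/3 = 48.
- Shortfall: 27 − 24 = 3 controls, with every Montreal control scanned.
- An expected 27 controls would need 27 × 3 = 81 Montreal participants.

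**Chance of at least 27 Montreal controls.** The article does not say how the 2:1 ratio is held, so three cases were taken:
- Simple randomisation: X ~ Binomial(72, 1/3), P(X ≥ 27) = 0.263.
- A fixed list of 48 controls among 144, not stratified by site: X ~ Hypergeometric(144, 48, 72), P(X ≥ 27) = 0.188.
- 2:1 held exactly within site: X = 24, so P = 0.

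**Alternative reading, 27 Music plus 27 Spanish.** This needs 54 Montreal intervention participants against 48 expected. With Binomial(72, 2/3), P(X ≥ 54) = 0.082, before asking for an even split between the two activities. It would also leave no controls in the imaging subset.

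**Precision of splits the design can deliver.** For a two-group difference with equal SD, the standard error is SD × √(1/n₁ + 1/n₂):

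| Split (intervention:control) | √(1/n₁ + 1/n₂) | Relative to 27:27 |
|---|---|---|
| 27:27 | 0.2722 | reference |
| 30:24 | 0.2739 | 0.2739/0.2722 = 1.006 |
| 36:18 | 0.2887 | 0.2887/0.2722 = 1.061 |

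The 36:18 row is what 54 participants chosen without regard to arm would give on average: 54 × 2/3 = 36 and 54 × 1/3 = 18.

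**Which scans are analysed.** Procedure and the Fig. 1 legend schedule MRI for everyone at PRE and F24, and at F4 for a subgroup only. Brain structure ties the structural outcome to the 54. The analysis section lists the structural measures without that limit and says that mixed models use all available data. Read together, these do not settle whether PRE and F24 scans from the other 144 − 54 = 90 participants are used.

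**The case against.** The strongest reply is that 24 is an expectation and not a ceiling. With individual allocation from random lists and no stated site stratification, Montreal could receive 27 or more controls. That stands, and it rules out saying that the figure cannot be met. A planned subset size should still be one that the design is expected to produce, and here the chance is about one in four at best and requires every Montreal control to be scanned.

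A second reply is that the loss is small: moving from 27:27 to 30:24 changes the standard error by 0.6%, on a secondary outcome. That also stands and limits how much weight the point carries.

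Three stronger readings are tempting, and the article does not support them.

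- **Attrition.** A reader might apply the expected 18% loss (24 × 0.82 = 19.7 controls; probability of at least 27 retained about 0.04) and call the target out of reach. The article does not say that 27 is a retained number; it may be the number entering imaging.
- **Selection by staff.** A reader might infer that staff will pick whom to scan by arm. The article does not describe how the subset is chosen, so what can be said is that a rule is needed.
- **Discarded scans.** A reader might infer that the structural analysis wrongly ignores 90 scanned participants. A subgroup with all three scans is a coherent design, and the analysis section does not confine the model to the 54. Any claimed power gain from pooling sites would rest on assumed retention and on equal variance across scanners, while Brain structure describes only the Montreal scanner. Pooling is a design preference and does not correct an error.

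**Conclusion.** The point holds as a mismatch of stated counts. The design is expected to supply about 24 Montreal controls against the 27 stated, a shortfall of 3, and neither reading of the phrase that yields 54 fits the planned numbers. The chance of reaching 27 controls is 0 to about 0.26, depending on how the 2:1 ratio is held. This assumes that exactly half of the 144 are recruited in Montreal and that every Montreal control is scanned; any refusal would lower the chance.

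The consequence is modest: a secondary imaging outcome, with little loss of precision once the split is restated. The primary outcome and its sample size are untouched. The uncertainty about scans from outside the 54 is an ambiguity between sections, to be reconciled, and not an arithmetic error.

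**What to change.** Restate the imaging subset at a size and split the design can deliver, and pre-specify how its members are chosen. Two options:

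1. **All Montreal controls (expected about 24) plus about 30 Montreal intervention participants** taken from a pre-generated random list, that is 30/48 = 62.5% of those expected. The total stays near 54 and the standard error is about 0.6% larger than 27:27. State what happens if the number of controls differs from 24. This option needs the arm to be known before the baseline fMRI, so the independent allocation office should hold the list and evaluators should not see it.
2. **54 Montreal participants chosen without regard to arm**, giving about 36:18. The standard error is about 6% larger than 27:27, but selection needs no knowledge of allocation.

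Also add one sentence, consistent across Procedure, the Fig. 1 legend, Brain structure and the analysis section, stating whether PRE and F24 structural scans from participants outside the 54 enter the structural analysis.

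The cost is revised wording and a selection list. Neither option needs more than about 54 participants in the subset.
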